
#### HEP Intervention

Topics for the HEP (active control group) sessions were identified so that they would not confound the overall objectives of the RiSE program [94]. Experienced speakers (eg, dietitian, pharmacist, and aesthetician) will facilitate the HEP classes in their area of expertise. Classes will focus on wellness promotion with topics that will include cooking organically, immunizations, and skincare.

Importantly, the RiSE intervention will be delivered using standardized materials by the same 2 experienced RiSE interventionists for all cohorts [95]. Participants are assigned weekly homework and maintain logs of their practice time. Strategies to monitor participant understanding and application of treatment include a weekly review of participant self-monitoring logs that document weekly practice. Facilitators will assess the understanding of RiSE skills by asking questions, discussing material with participants, and monitoring skills development during in-class practice. Participants complete a brief post-RiSE evaluation form to provide feedback regarding the use of RiSE skills during appropriate life situations. We will assess and control for group cohesion using the 5-item Engaged Scale from the Group Climate Questionnaire–Short Form [96,97]. The fidelity of the HEP control intervention will follow the methods proposed by Stanton et al [98] and will be similar to that of the treatment group. Session content will be reviewed and approved by principal investigators. Standardized PowerPoint (Microsoft Corporation) presentations and class materials will be used. Multiple mechanisms will be used to ensure the integrity of the RiSE and control interventions. These mechanisms support the 5 dimensions of intervention integrity formulated by Dane and Schneider [99]: adherence (the extent to which program objectives are met), quality of delivery (interventionist effectiveness), exposure (dosage), participant responsiveness (engagement), and program differentiation. Adherence to program objectives will be monitored using multiple informants and methods to collect integrity data. Interventionists will complete a self-evaluation checklist after each weekly session identifying the extent to which session objectives were met. The study team will review notes for patterns or any areas that need to be addressed.

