**Exclusion criteria**
History of myocardial infarction or ischemic heart disease and angina pectoris, stent placement, coronary artery bypass, left ventricular hypertrophy, congestive heart failure, or ischemic strokeAny major immune-related disease (eg, rheumatoid arthritis or lupus)Use of immune-altering medications, such as glucocorticoidsPeriodontal disease, bleeding gums, and dental work in the past 72 hCurrent smoker or has smoked in the past 3 moActive cancerActive infectionSubstance abuseCognitive or psychiatric disorder that would affect the ability to participate in program classes (Brief Screen for Cognitive Impairment total score of ≥8)

Participants will be assessed for CMD risk. They will also be assessed for cognitive impairment using the 3-item Brief Screen for Cognitive Impairment [71]: a total score of ≥8, which suggests cognitive impairment, will lead to the exclusion of the participant from the study. All ineligible participants will receive a gift card (US $10) after the screening. Baseline measures will be collected after the screening.

After the baseline interview (T0), eligible participants will be randomized 1:1 to RiSE or HEP, with each wave of enrollment treated as a block. The randomization plan (PROC PLAN) generated in SAS 9.4 (SAS Institute Inc) includes the site as a stratifying variable, and we plan for each site to have at least 6 RiSE and 6 control participants per wave. Patient registration data, group assignment, and self-report survey data will be managed via a single REDCap (Research Electronic Data Capture; Vanderbilt University) server with access for both sites.

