### Intervention

#### Overview

Both RiSE and HEP groups will meet weekly on Zoom (Zoom Communications, Inc) for 8 consecutive weeks for approximately 2 hours per session. In addition, 2 sessions will occur 1 month and 2 months after the completion of the interventions. These booster sessions will include a brief review of information covered during the programs and will allow the participants the opportunity to discuss and ask questions about how they applied what they learned in their lives. For every class attended, participants will receive a US $30 gift card. Participants will be sent an SMS text message or email reminder before each class. The RiSE and HEP classes will meet synchronously over Zoom and will be led by experts in the area. The study staff will review how to access Zoom with research participants at the baseline data collection appointment and will answer any questions they may have. The topics of each session are detailed in Table 2. Written educational materials will be provided to support the classes in both interventions.

**Table 2 table2:** Overview of the Resilience, Stress, and Ethnicity (RiSE) intervention and health education program (HEP) topics.

Session	RiSE program (intervention)	HEP (active control)
1	Introduction to RiSE; establish group as safe place for dialogue about racism and oppression	Introduction to HEP
2	Explore issues related to being a woman from a minoritized community and impact of intersectionality; discuss insidious forms of racism	Caring for your skin cleansers and makeup
3	Explore challenges in having conversations about race and racism and discuss how defensiveness makes conversations unproductive	Cooking organically
4	Identify both overt and covert racism; reflect how racism can affect emotions and esteem	Finding credible health care information on the web
5	Identify aversive racism, institutional racism, and the role of White privilege; reflect on how these forms of racism can affect emotions and esteem	Immunizations for adults—what is available and what do you need?
6	Describe the use of cognitive behavioral theory to conceptualize emotional reactions to race-based stress	Over-the-counter medications: potential hazards
7	Review physical reactions to stress; practice strategies to cope with stress	Growing an herb garden
8	Review resilience, coping, and empowerment in response to race-based stress	Communicating with the health care team

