#### RiSE Intervention

The RiSE intervention was adapted by [name] and [name] ([name], unpublished data, November 2017) for a behavioral health setting using components from an open-ended intervention developed by Carlson et al [35]. During our pilot work, the intervention was provided face-to-face and was tailored to help African American women address the unique challenges of navigating >1 marginalized identity (ie, intersectionality) [83]. RiSE includes three main components: (1) processing and sharing experiences associated with race-based stress, (2) psychoeducation related to the biopsychosocial impacts of racism, and (3) skill building and empowerment [48]. The intervention is feasible and well accepted among African American women [55]. In the first several sessions, RiSE provides participants with a safe place to share the emotional impact of race-based stress and to offer supportive listening among others in the group. Participants discuss their experiences as African American women, considering the ways in which the interaction between their racial and gender identities shapes their experiences. Facilitators promote discussion related to addressing racism and the unique experiences of Black women (eg, being stereotyped as angry and being expected to embody the “strong Black woman” archetype) [84-86] at interpersonal and structural levels. The facilitators share evidence of strategies to promote effective communication and internal emotional regulation regarding experiences of racism. Next, participants are provided with information on how racism can be manifested and are encouraged to use a common language with which to discuss their experiences. The facilitators provide psychoeducation on intersectionality, structural racism [87], overt racism [88], microaggressions [89], and internalized racism [90]. In addition, the facilitators assist participants in using cognitive behavioral strategies to understand thoughts, feelings, and actions associated with their experiences. Finally, the facilitators teach participants about stress, anxiety, and the “alarm” system [91] as they pertain to race-based stressors and other chronic stressors. Participants are encouraged to use adaptive coping strategies as well as community-based and cultural coping strategies. Throughout the program, participants engage in self-monitoring of the practice of skills discussed during the group sessions. Participants are sequentially introduced to the empowerment process steps [45] through journaling homework. Several mechanisms are key to the RiSE intervention in alleviating stress-related symptoms [48]. First, the group-based format allows participants to share their experiences with others and verbally process traumatic events [92]. Shame is believed to be a key barrier to overcoming race-based trauma [93]. Allowing participants to share their inner thoughts and concerns in a safe environment permits them to process their experiences and gain emotional validation from their peers. In addition, cognitive restructuring surrounding race-based trauma is used. This helps the participants reshape the maladaptive beliefs, such as self-blame, internalized stigma, and hopelessness, associated with their experiences. Participants learn that they do not cause racial and gender-based discrimination; rather, their experiences are related to systemic racism [35]. Participants are also encouraged to discuss their methods of coping with discrimination and are taught the difference between unhealthy and healthy coping strategies. The facilitators share approaches, such as mindfulness, cognitive restructuring, and advocacy, that participants can use to cope with their experiences [35]. Finally, participants are empowered to identify the meaning of their experiences and celebrate successes in using adaptive coping strategies. Classes are facilitated by 2 clinical psychologists trained in RiSE and who have >5 years of experience facilitating the RiSE program. In addition, they are experienced in leading and managing group dynamics and will develop ground rules with participants in the first session, including how to ensure that all participants can participate in the discussion.

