**Covariates and descriptive measures**						
	Early life adversity: Childhood Trauma Questionnaire [114]		✓			
	Ethnic identity: Vancouver Index of Acculturation [115]		✓			
	Health behaviors, anthropometrics, and brief medical history: Block Brief 2000 Food Frequency Questionnaire [116]; National Institute of Nursing Research Social Determinants of Health Survey [117]; Self-Administered Comorbidity Questionnaire [118]; blood pressure, height and weight, body fat percentage, and body water percentage [119]; Alcohol, Smoking, and Substance Involvement Screening Test [120]; Life Events Checklist-7 [121]; and Race-Related Events Scale [122], health behaviors, anthropometrics, brief medical history, and demographics		✓	✓	✓	✓
	Intervention and active control group cohesion: 5-Item Engaged Scale from Group Climate Questionnaire [96]			✓	✓	✓

^a^T0: baseline.

^b^T1: midintervention.

^c^T2: intervention completion.

^d^T3: 6 months after intervention completion.

^e^PROMIS: Patient-Reported Outcomes Measurement Information System.

^f^CRP: C-reactive protein.

^g^TNF-α: tumor necrosis factor–alpha.

^h^IL-6: interleukin-6.

^i^IL-1β: interleukin-1beta.

^j^IFN-γ: interferon-gamma.

^k^CRP is not measured using the Luminex Performance High Sensitivity. Cytokine Magnetic Panel B MultiPlex but rather an Enzyme-Linked Immunosorbent Assay kit from R&D Systems.

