#### Covariates

Several variables may influence or moderate the relationship between the intervention group and chronic stressors, stress-related symptoms, and inflammatory burden and coping mechanisms. For this reason, data on age, education, income, employment, height and weight, blood pressure, health behaviors, and early life adversities, as well as a brief medical history, will be collected at baseline and considered as covariates.

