#### Statistical Analysis

Baseline demographics and clinical characteristics will be reported according to the CONSORT (Consolidated Standards of Reporting Trials) guidelines. The size of any chance group imbalances will be described, but no formal significance testing of group differences will be performed [124]. Generalized linear mixed models (GLMMs) will be used for analyses of outcomes due to their flexibility regarding the distribution of dependent variables (DVs) and their superiority over alternative approaches such as repeated measures ANOVA for longitudinal modeling with missing data. Data will be collected from participants at 4 time points (T0: baseline, T1: midintervention; 4 wk, T2: intervention completion; 8 wk, and T3: 6 mo after intervention completion). Time will be modeled as a fixed effect, and random intercepts and random slopes will be considered to account for within-individual differences and trends. The primary DVs include stress-related symptoms (current perceived stress, depressive symptoms, fatigue, and sleep disturbance) and biomarkers (ie, IL-6, TNF-α, IL-1β, IFN-γ, and CRP) to be modeled using GLMM. Before modeling, DVs will be plotted to choose an optimal distribution and link function for GLMMs and to identify potential floor or ceiling effects. For each DV, a GLMM will regress the follow-up DV on a group×time interaction, the baseline value of the DV, and covariates. Treatment assignment (group) will be a fixed effect, and adjusted means with SEs will be used to describe group differences. Random effects will be evaluated for site and cohort. Exploratory end points include coping (Ways of Coping Questionnaire and Coping with Discrimination Scale), internalizing racism (Appropriated Racial Oppression Scale), and resistance to racism (Resistance and Empowerment Against Racism), which will be DVs in separate GLMMs, as described earlier.

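### Group cohesion is to be controlled for although it is measured only after randomization; this conflicts with the baseline-only Covariates section and, if followed, changes the effect being estimated

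*Protocol article*

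**What the plan says.** The commitment is in the protocol article under HEP Intervention, in the text on fidelity: "We will assess and control for group cohesion using the 5-item Engaged Scale from the Group Climate" Questionnaire. Table 3 places the scale in its block of covariates and descriptive measures, for both arms: "Intervention and active control group cohesion: 5-Item Engaged Scale from Group Climate Questionnaire". The row is ticked at T1, T2 and T3 and blank at T0.

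On timing, Procedures states: "After the baseline interview (T0), eligible participants will be randomized 1:1 to RiSE or HEP".

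The Covariates section lists demographic, clinical, behavioural and early-life variables that "will be collected at baseline and considered as covariates". Cohesion is not on that list.

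Under Statistical Analysis, for each outcome "a GLMM will regress the follow-up DV on a group×time interaction, the baseline value of the DV, and covariates". Covariates are then reduced to a smaller set, partly by how strongly they are associated with the outcome. No rule there limits the candidates to variables measured before randomization. The same section commits to intent-to-treat analysis.

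On how RiSE works, the RiSE Intervention section gives as the first of its key mechanisms that "the group-based format allows participants to share their experiences with others and verbally process traumatic events", and goes on to validation from peers. In Table 2, RiSE session 1 is to "establish group as safe place for dialogue about racism and oppression"; HEP session 1 is only an introduction.

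**The concern.** A covariate in a randomized comparison should be fixed before allocation. Cohesion cannot be: the class groups do not exist at T0, and the scale is completed during or after treatment. Two things follow if it is placed beside the group term.

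First, the target changes. The group coefficient becomes the difference between arms at equal cohesion, not the total effect of being assigned to RiSE rather than HEP. If part of RiSE's benefit comes through the group, that part is taken out of the estimate.

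Second, randomization no longer protects the comparison. Women who report high engagement may differ in mood or social support, and these also affect perceived stress. Conditioning on cohesion can bring that confounding into the arm contrast.

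A smaller matter is missing scores. A woman who stops attending classes but still comes to assessments may have no meaningful cohesion score. A complete-case adjustment could then drop her although her outcome is known.

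**Working it through.** **1. Timing.** Randomization follows T0, and cohesion is scheduled at T1 (4 weeks), T2 (8 weeks) and T3 (6 months after completion). All three scores are post-randomization.

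**2. Consistency.** The fidelity text says cohesion will be controlled for, and Table 3 groups it with covariates. The Covariates section describes baseline collection and omits it. Statistical Analysis refers only to covariates in general. Nothing confines the cohesion adjustment to a fidelity, mediation or sensitivity analysis.

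**3. The plan's own power figure.** Inputs from Sample Size: 125 per arm with follow-up, difference 3 points, SD 10, covariate R-squared 0.3, alpha 0.05.

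- Residual SD = 10 × √(1 − 0.3) = 8.367
- SE of the difference = 8.367 × √(2/125) = 1.058
- Power: 0.809 by the normal approximation and 0.806 by the F test with 1 and 243 degrees of freedom

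This reproduces the stated power of more than 80%. The normal formula needs 123 per arm, so there is almost no reserve.

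**4. A fixed loss (assumed).** Suppose each SD of cohesion lowers the stress score by 2 points, and RiSE groups exceed HEP groups by 0.25 or 0.5 SD. Adjustment then absorbs 0.25 × 2 = 0.5 or 0.5 × 2 = 1.0 point. With the SE held at 1.058 and the noncentral t:

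| Points absorbed | Remaining difference | Power |
|---|---|---|
| 0 | 3.0 | 0.81 |
| 0.5 | 2.5 | 0.653 |
| 1.0 | 2.0 | 0.469 |

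If the SE is also updated for the variance that cohesion explains and for its imbalance between arms, SE = √(70 − 2²) × √(2/125) × √(1 + a²/4). This is 1.036 for a = 0.25 and 1.059 for a = 0.5. Power by the normal approximation is then about 0.68 and 0.47, so the picture is the same.

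**5. A wider range (assumed).** Let *a* be the RiSE-minus-HEP difference in cohesion, in within-arm SDs. Let *r* be the size of the within-arm correlation between higher cohesion and lower residual stress score.

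- Adjusted difference = 3 − r × 8.367 × a
- SE = 8.367 × √(1 − r²) × √(2/125) × √(1 + a²/4)
- Power by the normal approximation

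| a | r | Adjusted difference | Power |
|---|---|---|---|
| 0.2 | 0.1 | 2.83 | 0.76 |
| 0.3 | 0.2 | 2.50 | 0.66 |
| 0.5 | 0.3 | 1.75 | 0.39 |
| 0.8 | 0.3 | 0.99 | 0.15 |

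With a = 0 the difference stays at 3 points. With the sign reversed, a = −0.3 and r = 0.2, it becomes 3 + 0.2 × 8.367 × 0.3 = 3.50, which overstates the total effect. The documents give neither *a* nor *r*.

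**The case against.** The best defence is that the article never puts cohesion into the efficacy model. The sentence sits among fidelity procedures, engagement is one of the integrity dimensions listed there, and the instrument measures engagement. Table 3's block covers descriptive measures as well as covariates, the Covariates section is limited to baseline, only a subset of covariates will be used, and a detailed analysis plan is still to come. This stands in part: adjustment of the primary model is not certain. But the sentence speaks of controlling for a variable by means of a questionnaire score, and statistical adjustment is its natural reading. The baseline-only section contradicts that sentence without withdrawing it. The point is also not an omission that an analysis plan will fill; it is a statement that a plan could carry forward.

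Four stronger readings are tempting, and the documents do not support them.

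- A reader might infer that RiSE is designed to raise cohesion above HEP. No text says so. Both arms meet weekly in groups, for sessions of similar length, with booster sessions. The variable named as hypothesized mediator, under Sample Size, is coping. That cohesion lies on the pathway is a plausible inference from the mechanism text, not a stated fact.
- A reader might infer that the bias must be toward no effect. That needs more cohesive RiSE groups and a link from cohesion to lower stress. With no arm difference there is no shift in the calculation above; with more cohesive HEP groups it reverses; confounding can act in either direction.
- A reader might infer that women lost before T1 would be dropped because of the adjustment. They contribute no follow-up outcome in any case. The loss specific to cohesion is limited to women who leave the classes but attend assessments, and the article does not say whether they would lack a score.
- A reader might infer that a random effect for class group already covers shared group influence. The plan evaluates random effects only for site and cohort.

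**Conclusion.** The point holds as a conflict in the text with a real consequence if the fidelity sentence is followed. The documents establish that cohesion is always measured after randomization, that one section says it will be controlled for, and that another describes baseline covariates without naming it. If it enters the outcome models, the group coefficient is no longer the total intent-to-treat effect, whatever the size of the shift.

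Size and direction are not known from the documents. The fall in power from about 81% to between about 65% and 47% rests on an assumed loss of 0.5 to 1.0 of the 3 points; other assumptions give less, more or the opposite shift. The planned sample size reproduces and is not affected.

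**What to change.** Under HEP Intervention, change the commitment so that cohesion is *assessed and reported by arm* rather than controlled for. Under Statistical Analysis, state, in line with the Covariates section, that only variables measured before randomization are eligible as covariates in the efficacy models. In Table 3, mark the Engaged Scale as a descriptive or fidelity measure. Use cohesion only for fidelity description or in an exploratory mediation analysis labelled as such.

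The change should stand on its own and not rely on a random effect for class group, which the plan does not contain.

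The cost is a sentence or two and a table label. Data collection, schedule and sample size do not change. It should be settled before the statistical analysis plan is finalized.

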### Outcome Variables

The outcome variables for the trial include stress-related symptoms (current perceived stress, depressive symptoms, fatigue, and sleep disturbance) and inflammatory burden (as indicated by biomarkers such as IL-6, TNF-α, IL-1β, IFN-γ, and salivary CRP; Table 3). Each of these variables will be collected at 4 time points: T0, T1, T2, and T3.

**Table 3 table3:** Study measures.

		Enrollment	T0^a^	T1^b^	T2^c^	T3^d^
**Eligibility**						
	Eligibility screening questions	✓				
	Brief Screen for Cognitive Impairment [71]	✓				
